## Abstract

**Background:**

Distal radius fractures are among the most common fractures and account for approximately one-sixth of all fractures diagnosed. Therapy results after distal radius fracture, especially of elderly patients, are often suboptimal. The inevitable immobilization for several weeks leads to reduction in range of motion, deterioration of muscle strength, malfunction of fine motor skills as well as changes of motor and sensory representations in the brain. Currently, there are no strategies to counteract these immobilization problems. The overall aim of the study is to investigate the therapeutic potential of motor-cognitive approaches (mental practice or mirror therapy) on hand function after wrist fracture.

**Methods/Design:**

This study is a controlled, randomized, longitudinal intervention study with three intervention groups. One experimental group imagines movements of the fractured upper extremity without executing them (mental practice). The second experimental group receives a mirror therapy program consisting of the performance of functional movement synergies using the unaffected forearm, wrist, and hand. The control group completes a relaxation training regime. Additionally, all patients receive usual care by the general practitioner. We include women aged 60 years and older having a distal radius fracture and sufficient cognitive function. All groups are visited at home for therapy sessions 5 times per week for the first 3 weeks and 3 times per week for weeks 4 to 6. Measurements are taken at therapy onset, and after 3, 6 and 12 weeks. The primary outcome measure will assess upper extremity functioning (Patient-Rated Wrist Evaluation [PRWE]), while secondary outcome measures cover subjective wrist function (Disabilities of the Arm and Shoulder; [DASH], objective impairment (range of motion, grip force) and quality of life (EuroQol-5D, [EQ5D]).

**Discussion:**

Results from this trial will contribute to the evidence on motor-cognitive approaches in the early therapy of distal radius fractures.

**Trial registration:**

The trial is registered at ClinicalTrials.gov with registration number NCT01394809 and was granted permission by the Medical Ethical Review Committee of the University of Tübingen in June 2011.

**Electronic supplementary material:**

The online version of this article (doi:10.1186/1471-2474-15-287) contains supplementary material, which is available to authorized users.

## Background

Distal radius fractures are among the most common osteoporotic fractures[1] and account for an estimated 17% of fractures treated in US emergency departments[2] with a female–male ratio of about 3:1[3]. Corresponding to the demographic development, osteoporotic fractures of the wrist, humerus spine or hip can be expected to increase further in the coming years and with it the burden on healthcare resources[4, 5]. Regardless of the fact whether these fractures are treated surgically or by casting, patients are at least immobilized for two to six weeks or more. Physical and occupational therapy as a key element in rehabilitation starts after the removal of the fixation device. However, during the period of fixation, patients often keep their injured hand in rigid postures, in which the volar plates and adjacent ligaments of the digital joints are shortened[6]. Different methods of treatment, but especially the long immobilization periods lead to overall complication rates ranging from 6 to 80% and have been associated with poor functional outcomes[7]. These complications not only include complex and regional pain syndrome, stiffness, nerve injury, tendon and ligament injuries, but a massive reduction in range of motion (ROM), muscular atrophy, and loss of movement representation[8]. As a result, the final hand function is often suboptimal[9]. Previous studies have indicated that 20% of patients with distal radius fracture had persistent symptoms, and 10% continued to have functional impairments after the typical recovery period[10]. In a study by consortium partners we demonstrated that the risk of losing independence after a wrist fracture is almost as high as after a hip fracture[11]. This partly relates to upper extremity dysfunction with activities of daily living such as eating, getting dressed and washed.

The goal for rehabilitation after wrist fractures is to achieve complete and rapid recovery of ROM, strength, and function of the wrist and hand. Improvement of the functional outcome after wrist fracture can probably not only be found in changing the operative technique[12]. Hence, for improvement of functional outcome, one has to focus on the postoperative rehabilitation period[13, 14]. A patient would need a treatment procedure that is more active without actually stressing the bone and that may prevent from the negative side effects as well as from the central reorganization that takes place as a result of immobilization. This leads to a temporary forgetting of the function of the affected limb[15], and results in the inefficiency of the central control of movements. Immobilization has shown to result rather rapidly in changes of motor and sensory representations in the brain of peripheral organs such as finger, arm, or leg[16, 17]. For example, Langer et al.[16] showed a decrease in cortical thickness in the left primary motor and somatosensory area as well as a decrease in the grey matter in the left corticospinal tract after at least 14 days of limb immobilization.

Several studies have shown that sensory input does not exclusively result from actually performed movements. Imagined movements without actually moving the limbs (explicit motor imagery) as well as observational learning (mirror therapy) also generate sensory input[18–21]. Mirror therapy (MT), in which a mirror is placed in the patient's midsagittal plane, so that he/she can see his/her unaffected arm/hand as if it was the affected one, has mainly been studied for two different purposes: pain relief[22], and motor recovery post-stroke[23–25]. Furthermore, MT has been shown to increase ipsilateral primary motor excitability in healthy controls[26], which may account for the improvement in motor function. Mental practice (MP) represents a class of training or therapy regimes in which an internal representation of a movement is repeatedly simulated in mind from a first-person perspective, without actual physical movement, and is effective in motor recovery in neurological and orthopedic rehabilitation[27–29]. Proposed mechanisms for improved motor recovery with MT and MP include reconciliation of motor output and sensory feedback MT,[30] and graded activation of cortical motor networks MP,[31]. According to Jeannerod[32, 33] MP and the preparation of movements share common mechanisms and are functionally equivalent[34]. Furthermore, the activation of pre-motor “mirror neurons”, which have intimate connections with visual processing areas, is thought to prime the primary motor cortex and to be important in imitating motor action[35–37].

In orthopedic rehabilitation MP as well as MT has only received minor attention as a promising psychological complement to conventional physical therapy approaches. Three studies have examined the effects of MT in patients after hand surgery other than amputation[18, 38, 39]. While Rosén and Lundborg[38] reported three different cases (e.g. tendon repair) when MT was applied in combination with traditional hand training (no further details regarding the number of training sessions or duration were given), Altschuler and Hu[18] as well as Rostami et al.[39] examined hand function with different orthopedic conditions in one (insufficient information on intervention), respectively 12 patients (15 sessions à 30 minutes). Both studies conducted MT in combination with physical therapy. All three studies reported improvements in objective as well as subjective measures of hand function. None of these studies had the goal to overcome the effects of immobilization. There are mixed results on the effects of MP during disuse or immobilization[40–45]. Some researchers have found support for mental imagery to maintain muscle strength and flexibility[42, 44] Schott & Limberger: Effects of mental practice on gait after total hip endoprosthesis, in prep], while others have not[40, 41, 43, 45]. Methodological inconsistencies could account for many of the contradictory findings within the literature. Studies vary in the participants’ age and health status, the type of imagery, the content of imagery, as well as intervention length. Explicit imagery has been shown to create the greatest physiological benefits but only few studies specifically elaborate on their imagery script. Protocols for imagery intervention also varied among researchers from as little as 10 days to 7 weeks in duration with varying numbers of sessions per day. To our knowledge, only two studies examined the efficacy of explicit motor imagery and MT so far[42, 46]. Ietswaart and colleagues[46] found no enhanced improvement as a result of MP with motor imagery in upper hand function of stroke patients. Frenkel[42] examined the efficacy of a MP combined with MT after knee endoprothesis surgery, but only found significant results for the criterion flexion. No other studies exist with regard to patients with orthopedic injuries, comparing the efficacy of MT or MP.

The purpose of this randomized study is to determine whether explicit motor imagery or MT during the immobilization period after distal radius fracture results in a greater recovery of central aspects of hand function. The objective of this study is to establish the effectiveness of daily training of movement imagery with the affected arm (MP) or the healthy arm (MT). It will also be examined whether enhanced functional recovery of the hand due to MP or MT is also associated with increases in the amount of activities of daily living. It will be investigated whether the benefit of motor-cognitive approaches for distal radius fracture patients is related to their individual differences in motor imagery ability.

## Methods/Design

Post-fracture strategies that tackle the problems mentioned above might reduce the functional loss after wrist fractures and improve quality of life considerably. Currently, no proactive strategies are published to counteract the immobilization problems. Our participants are being recruited from different hospitals and randomly allocated to one of three groups. There are two experimental intervention groups (MP and MT) and one control group. We use two different strategies originally developed and tested for the rehabilitation of stroke patients: Participants either receive a MP or a MT program. This novel approach combines neuropsychological approaches with sport science and conventional physiotherapy.

The study is conducted as a randomized controlled trial. The purpose of the study is to examine the effects of MP and MT on upper extremity function after osteoporotic wrist fractures.

The trial is conducted in agreement with the principles of the Declaration of Helsinki, and with the guidelines of Good Clinical Practice (GCP). The study protocol was approved by the local and independent Ethics Committee Tübingen (Institutional Review Board).

### Procedure

All patients give written informed consent prior to the study. Before randomization, the patients complete the Controllability of Motor Imagery Test[47] to control for the ability to perform and control a mental image of a movement, which is essential for successful imagery training. After baseline assessment, randomization is performed by an independent department (Department of Biometrics at Ulm University).Assessment of primary and secondary outcomes takes place upon entry to the study (T1) by a blinded assessor and is repeated after 3 weeks (T2), 6 weeks (T3), and 12 weeks (T4, follow-up) after the beginning of the training program (see Figure 1).

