### Intervention

Participants in the experimental groups receive either a MP or a MT program. Patients in the control group are instructed to practice relaxation techniques. The intervention period lasts six weeks and takes place in the patient’s private home. Additionally, all patients receive therapy as usual. All MP and MT training sessions were provided by the same physical therapist; however, a second therapist conducted the primary and secondary evaluations. In week one to three the patient participates in five sessions per week on five consecutive days (Monday-Friday), and in week’s four to six the patient participates three times per week with the therapist and two times without. As of week 4, when the guided therapy sessions are reduced to 3 times per week, all patients receive written instructions containing descriptions and photos of the movement tasks. They are asked to document their training sessions (duration and level of difficulty) in daily training diaries. Additionally, the patients are supplied with an MP3-player with a text for progressive muscle relaxation. All therapy sessions are 45 minutes per treatment session. Each session (MP as well as MT) starts with a standardized progressive muscle relaxation focusing on wrist (healthy side) and other body parts (based on[49]), and is applied for five to ten minutes to aid the participant’s ability to concentrate on the internal body sensations of the following imagination protocol.

The content of the two motor-cognitive interventions (MP and MT) is based on a simplified version of Gentile’s task taxonomy[50]: four sections are defined by the combination of stationary/mobile performer with open/closed environment. The basic movement tasks in this study are dorsal extension, palmar flexion, radial and ulnar abduction as well as supination and pronation using Gentile’s Taxonomy of Tasks to structure the training content and progression ([51]; details provided in Table 1). Object manipulation and/or intertrial variability mark higher levels of difficulty. Patients are asked to rate the level of difficulty for mentally simulating the movement, respectively for perceiving the reflected image in the mirror as their affected side (1 very easy to 10 very hard). As soon as they rate a task with 4 (“reasonably easy”) or lower, they try a task of a higher difficulty level. For retaining same conditions, the patients should not execute the movement with the affected side during MP and MT.

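### The stated purpose is training while the wrist is immobilised, but a fixed six-week programme timed from training start cannot separate that from training after fixation removal, and fixation differences add variance to PRWE at T2 and T3

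*Protocol article*

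**What the plan says.** The protocol article describes its question in more than one way. The purpose paragraph that closes the Background asks whether "explicit motor imagery or MT during the immobilization period after distal radius fracture results in a greater recovery". The next sentence is broader: to "establish the effectiveness of daily training of movement imagery with the affected arm (MP) or the healthy arm (MT"). Methods/Design is broader again: "The purpose of the study is to examine the effects of MP and MT on upper extremity function after osteoporotic wrist fractures". The end of the Intervention section returns to the narrow view, giving the aim of the protocols as preserving the motor representation so that the hand performs well once the splint is off.

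The schedule is uniform. Under Intervention, "The intervention period lasts six weeks": five guided sessions a week in weeks 1 to 3, then three guided and two unguided a week in weeks 4 to 6, with usual therapy for everyone. Under Procedure, the repeat assessments are set at 3 weeks (T2), at 6 weeks (T3) and at "12 weeks (T4, follow-up) after the beginning of the training program".

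On immobilisation, the Background says that, with surgery or casting, "patients are at least immobilized for two to six weeks or more", and that "Physical and occupational therapy as a key element in rehabilitation starts after the removal of the fixation device". The visible text ties neither the length of training nor any visit to fixation removal.

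**The concern.** The narrow purpose names an exposure, training given while the wrist is fixed. The schedule delivers a different one, six weeks of training whatever the state of the wrist. If fixation lasts as long as the Background says, some patients do most of their sessions with a free wrist and with usual therapy under way, while others do nearly all of them splinted.

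Two things follow. First, a positive result could come from training during immobilisation, from training added to ordinary rehabilitation, or from both, and the design cannot tell which. Second, PRWE asks about pain and difficulty in daily tasks such as lifting and buttoning. Those answers plausibly depend on whether the wrist is splinted and how long it has been free, so values taken at the same visit come from different points of recovery. With 13 patients per arm, that extra variance matters.

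**Working it through.** The plan gives no figure on this point to reproduce. The check sets the schedule against the Background's own immobilisation range.

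**1. Sessions done while immobilised** (counts from Intervention)

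- Guided: 5 × 3 + 3 × 3 = 24. Unguided: 2 × 3 = 6. Total: 30, or 5 per week.
- Sessions before removal, if fixation ends *w* weeks after training start: 5 × *w*, for *w* up to 6.

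| Removal after training start | All sessions | Guided sessions |
|---|---|---|
| 2 weeks | 10 of 30 (33%) | 10 of 24 (42%) |
| 3 weeks | 15 of 30 (50%) | 15 of 24 (63%) |
| 4 weeks | 20 of 30 (67%) | 18 of 24 (75%) |
| 6 weeks | 30 of 30 (100%) | 24 of 24 (100%) |

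**2. State of the wrist at T2 and T3**

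The document gives neither the distribution of immobilisation time nor the lag from fixation to training start. Assumptions: duration *D* is uniform from 2 to *h* weeks, with *h* = 6 (the stated range) or *h* = 8 (one reading of the open upper end); the lag *L* is 0 to 2 weeks.

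- Share still immobilised at T2 = P(*D* − *L* > 3) = (*h* − 3 − *L*)/(*h* − 2)
- Share still immobilised at T3 = P(*D* − *L* > 6) = max{0, (*h* − 6 − *L*)/(*h* − 2)}
- Mean share of the programme spent immobilised = E[min(*D* − *L*, 6)]/6

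| *h* | *L* | Immobilised at T2 | Immobilised at T3 | Mean share of programme immobilised |
|---|---|---|---|---|
| 6 | 0 | 3/4 = 75% | 0% | 67% |
| 6 | 1 | 2/4 = 50% | 0% | 50% |
| 6 | 2 | 1/4 = 25% | 0% | 33% |
| 8 | 0 | 5/6 = 83% | 2/6 = 33% | 78% |
| 8 | 1 | 4/6 = 67% | 1/6 = 17% | 65% |
| 8 | 2 | 3/6 = 50% | 0% | 50% |

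T2 is mixed in every scenario. At T3 no wrist is still fixed unless immobilisation exceeds six weeks. What varies at T3 is time since removal: a patient freed at week 2 of training has had 6 − 2 = 4 weeks, one freed at week 6 has had 6 − 6 = 0.

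**3. How uneven the arms could be by chance**

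Assumptions: a fraction *p* of patients has short fixation; 13 per arm; simple randomisation, which the article does not state. Arm counts are then independent Binomial(13, *p*).

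| *p* | Two given arms differ by 4 or more patients | Largest and smallest of three arms differ by 4 or more |
|---|---|---|
| 0.5 | 0.169 | 0.353 |
| 0.3 | 0.132 | 0.287 |

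Four of 13 is 31 percentage points. These are headcounts. They show that an uneven split is not rare, but not how many PRWE points it would be worth.

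**The case against.** The strongest reply is that the broader wording in the Background and in Methods/Design is the real question, and that the randomised comparison of six weeks of training against relaxation answers it. Usual care is common to all arms, controls receive matched therapist time, and T4 comes six weeks after training ends. Timing visits from training start is normal, and fixation removal happens after randomisation, so anchoring visits to it would bring problems of its own. All of this stands.

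A reader might infer more than the document supports in four places:

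- **That T3 also mixes splinted and free wrists.** This rests only on the open upper end of the Background's range. Within two to six weeks, nobody is still immobilised after six weeks of training.
- **That the trial's objective goes only partly tested.** That holds for the immobilisation-period purpose alone, not for the broader statements.
- **That chance imbalance biases the result.** Randomisation leaves the comparison unbiased in expectation, and the test's error rate already averages over such imbalances. The cost is precision.
- **That nothing is balanced or adjusted.** The article is silent, and such detail commonly sits in the full protocol or analysis plan. The exclusion list is incomplete in the text at hand and Figure 1 is not shown, so a limit on fixation type or entry time may exist.

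The Background range is also a general statement, not a description of the enrolled patients. What survives is that the article itself fixes a programme length and a visit clock that do not follow the exposure named in its purpose. A limit on fixation type would not remove that mismatch.

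**Conclusion.** The point holds as a mismatch between one stated purpose and the schedule, with a loss of precision; it does not make the trial invalid. The effect of the whole six-week programme can be estimated. The effect of training during immobilisation cannot be separated from that of training after it. If immobilisation runs two to six weeks and training starts within two weeks of fixation, 25% to 75% of wrists would still be fixed at T2, none at T3, and on average 33% to 67% of the programme would be spent immobilised. Those ranges assume a uniform spread and the lags shown. The added variance in PRWE at T2 and T3 cannot be sized, because the document gives nothing that links fixation to PRWE.

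**What to change.** 1. Take the injury date and fixation type (surgical or cast) from the hospital record at T1, which precedes randomisation. Prespecify fixation type as a baseline covariate in the PRWE analysis and, if degrees of freedom allow, days from injury to T1.
2. Record the actual date of fixation removal and the start of usual physical therapy. Report sessions completed before removal by arm, descriptively. Do not adjust for these variables, since they arise after randomisation.
3. Reconcile the purpose in the Background with the fixed programme under Intervention. Word the conclusion as the effect of a six-week early MP or MT programme during and after immobilisation, unless the data show that nearly all sessions fell before removal.

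The cost is a few dates and one category per patient, retrievable for those already enrolled; one or two of the 39 − 3 = 36 between-patient error degrees of freedom; and a narrower conclusion. No extra visits or patients are needed. Stratifying the remaining allocation is not recommended. The Discussion reports two withdrawals as under 10%, which implies more than 20 enrolled and so at most 18 of 39 still to allocate, too few across three arms to justify changing the randomisation.

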**Figure 1 Fig1:**
[figure not shown]
**Flow diagram of study design.**

### Participants

We include females aged 60 years and older with a distal radius fracture. We exclude persons with the following characteristics:

Unstable medical conditions which preclude surgical intervention (ASA 5)Patients with an open fractureAssociated soft tissue or skeletal injury to the same limbCognitive impairment 6CIT[48],

### Intervention

Participants in the experimental groups receive either a MP or a MT program. Patients in the control group are instructed to practice relaxation techniques. The intervention period lasts six weeks and takes place in the patient’s private home. Additionally, all patients receive therapy as usual. All MP and MT training sessions were provided by the same physical therapist; however, a second therapist conducted the primary and secondary evaluations. In week one to three the patient participates in five sessions per week on five consecutive days (Monday-Friday), and in week’s four to six the patient participates three times per week with the therapist and two times without. As of week 4, when the guided therapy sessions are reduced to 3 times per week, all patients receive written instructions containing descriptions and photos of the movement tasks. They are asked to document their training sessions (duration and level of difficulty) in daily training diaries. Additionally, the patients are supplied with an MP3-player with a text for progressive muscle relaxation. All therapy sessions are 45 minutes per treatment session. Each session (MP as well as MT) starts with a standardized progressive muscle relaxation focusing on wrist (healthy side) and other body parts (based on[49]), and is applied for five to ten minutes to aid the participant’s ability to concentrate on the internal body sensations of the following imagination protocol.

The content of the two motor-cognitive interventions (MP and MT) is based on a simplified version of Gentile’s task taxonomy[50]: four sections are defined by the combination of stationary/mobile performer with open/closed environment. The basic movement tasks in this study are dorsal extension, palmar flexion, radial and ulnar abduction as well as supination and pronation using Gentile’s Taxonomy of Tasks to structure the training content and progression ([51]; details provided in Table 1). Object manipulation and/or intertrial variability mark higher levels of difficulty. Patients are asked to rate the level of difficulty for mentally simulating the movement, respectively for perceiving the reflected image in the mirror as their affected side (1 very easy to 10 very hard). As soon as they rate a task with 4 (“reasonably easy”) or lower, they try a task of a higher difficulty level. For retaining same conditions, the patients should not execute the movement with the affected side during MP and MT.

**Table 1 Tab1:** **Movement tasks based on Gentile’s taxonomy of tasks**[51]

		Body stability	
		No object manipulation	Object manipulation
		⇨ dorsal extension	⇨ lifting up weight (dorsal extension)
		⇨ palmar flexion	⇨ lifting up weight (palmar flexion)
		⇨ ulnar-/radial abduction	⇨ wiping a table with a cloth
		⇨ supination/pronation	⇨ handling of a bike lock/kitchen timer
	**No intertrial variability**	⇨ opening and closing hand (like grasping a cup)	⇨ wringing out a towel
		⇨ thumb-finger-oppositions	⇨ compressing a softball
		⇨ finger-tapping sequence	⇨ grasping a pen with little finger (e.g.) and thumb
			⇨ playing piano (simple 5-finger-scale)

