**Table 2 Tab2:** **Examples of mental practice script delivered to MP group**

Visual:	How does your hand look turning a door key? Imagine seeing your hand, the key, and the door. See your wrist turning and the forearm pronating.
**Kinesthetic:**	Imagine touching the cold metal of the key with your fingers. Now feel your muscles in your forearm and hand activate as you grasp and turn the key. What can you feel? Is there a tension in your muscles?

Active execution with the unaffected side (1 x with open eyes)Visual imagery (1 x unaffected side, 1 x affected side; with closed eyes)Active execution with the unaffected side (1 x with closed eyes)Kinesthetic imagery (1 x unaffected side, 1 x affected side; with closed eyes).

After establishing the internal concept of wrist movements, the systematic training phase with physical training alternating with MP follows this protocol:Active execution with the unaffected side (2 x with open eyes)Active execution with the unaffected side (2 x with closed eyes)Kinesthetic imagery with the unaffected side (1 x with closed eyes)Kinesthetic imagery with the affected side (5–10 x with closed eyes)

Due to the findings of Yae et al.[55], that mental imagery is most effective with a kinesthetic focus, our training process is aiming at that modality.

Patients in the MT group immediately start with the observation of the movements with the unaffected side in the mirror. During MT the affected hand remains hidden from view behind the mirror, which is placed in the midsagittal plane of the participant. The patient is observing the reflected image of the unaffected hand, which appears like the affected side performing the movement. Patients perform each wrist movement with the unaffected side 8 to 10 times with visual focus on the mirrored picture of the healthy side.

The overall aim of these protocols is to preserve motor representation of hand function to enable patients to execute wrist movements with high accuracy and appropriate strength after splint removal.

The control group receives relaxation training to achieve the same total amount of time the therapist spends with the patients of the experimental groups.

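### The week-4 hand-out and diary rule covers all patients, although the movement tasks and difficulty rating belong to the MP and MT arms and control patients are assigned relaxation

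*Protocol article*

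**What the plan says.** All places are in the protocol article.

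- **Control arm.** The Intervention section says "Patients in the control group are instructed to practice relaxation techniques". After Table 2 it gives the purpose: "The control group receives relaxation training to achieve the same total amount of time the therapist spends with the patients of the experimental groups".
- **Schedule.** The abstract says "All groups are visited at home for therapy sessions 5 times per week for the first 3 weeks and 3 times per week" in weeks 4 to 6. The Intervention section adds the unguided sessions for those weeks: "three times per week with the therapist and two times without".
- **Hand-out.** From week 4, when guided sessions become fewer, "all patients receive written instructions containing descriptions and photos of the movement tasks". The next sentence has these patients keep a daily diary of session duration and difficulty. They also get an MP3 player with a relaxation text.
- **Movement tasks.** "The basic movement tasks in this study are dorsal extension, palmar flexion, radial and ulnar abduction as well as supination and pronation". This follows directly on a statement that the content of the two motor-cognitive interventions is built on a task taxonomy. Table 1 lists the tasks.
- **Difficulty rating.** It is a 1-to-10 rating of how hard it is to simulate the movement mentally, or to perceive the mirror image as the affected side. No rating is defined for relaxation.

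**The concern.** The control arm is meant to match the experimental arms on therapist time while differing in content. A hand-out rule that covers every patient cuts across this, because the sheets describe and picture the tasks that make up MP and MT training. The diary does the same: a control patient is asked to log a difficulty that has meaning only for imagery or the mirror.

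What is at stake is the separation between the experimental arms and control. If control patients work with the task sheets in their unguided sessions, and this helps them, the two comparisons that answer the trial's main question become smaller. With about 12 analysed patients per arm, there is little room to absorb that. If the sentence is only imprecise, the published description of the comparator is still wrong, and anyone repeating the trial from it would repeat the error.

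**Working it through.** The plan gives no figure to reproduce. The check is a comparison of passages, followed by simple counts.

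**1. Whom does the rule cover?** Shortly before the hand-out sentence, and just after the control group is introduced, the same paragraph says "Additionally, all patients receive therapy as usual". That must include control patients. The abstract uses the phrase in the same way, after describing the control regime: "Additionally, all patients receive usual care by the general practitioner". Where the paragraph means only the experimental arms, it names MP and MT, as it does for who provides the sessions and how each session starts. The event that triggers the hand-out, the drop to three guided sessions, applies to all groups. No sentence limits the sheets by arm or describes a different sheet for control. The literal reading is therefore all three arms.

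**2. Whose content is it?** Table 1 and the text around it tie the tasks to MP and MT. Description and instruction of wrist movements are also the first two steps of the MT and MP training protocol given after Table 1. The sheets thus carry part of the experimental content. They are not said to contain the imagery script or the mirror procedure.

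**3. How many sessions are involved?**
- Guided, weeks 1-3: 5 × 3 = 15
- Guided, weeks 4-6: 3 × 3 = 9
- Unguided, weeks 4-6: 2 × 3 = 6
- Total: 15 + 9 + 6 = 30; unguided share 6/30 = 20%

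The unguided sessions are stated for the patient without naming an arm; I assume they apply to control as well. On the literal reading, all three arms hold the same unguided-session materials: movement sheets, diary and relaxation recording.

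**4. Which time points?** Under Procedure, T2 is 3 weeks, T3 6 weeks and T4 12 weeks after the start of training. The sheets come from week 4, so T1 and T2 precede them. T3 and T4 follow.

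**5. Which comparisons?** Let Δ be the true difference between an experimental arm and an uncontaminated control arm at T3 or T4, and δ the shift in the control mean caused by the sheets, in the same direction as the intervention effect.
- MP − control becomes Δ(MP) − δ.
- MT − control becomes Δ(MT) − δ.
- MP − MT does not contain the control mean and is unchanged.

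δ depends on how many control patients use the sheets and on how much untaught use achieves. The documents give neither.

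**The case against.** The strongest reply is that the sentence is loose drafting and was written with MP and MT in mind. It stands between sentences about MP and MT sessions. A control patient has no movement task to document and no difficulty scale to use, so the instruction makes full sense only for the experimental arms. This reading is plausible, and the text does not show that any control patient received the sheets. It does not remove the contradiction, because nothing limits the hand-out and the same phrase covers all arms nearby.

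It is also fair to say that the article never calls the control relaxation *only*, and that a condensed article may leave a control hand-out to the full protocol. The absence of such a hand-out is not the point here. The point is a stated rule that conflicts with the stated arm content.

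Stronger readings are tempting and are not supported:

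- **That control patients receive the intervention.** MP as described needs guided verbalising, key characteristics and alternating execution and imagery; MT needs a mirror. The sheets transfer task content, not the technique.
- **That photos alone have an effect.** The Background speaks of imagined movements and mirror-based observation. It makes no claim about still pictures.
- **That the contrast is diluted by up to 20%, with a matching loss of power.** 20% is a share of sessions. Turning it into dilution of that size through those sessions would require control patients to perform every unguided session as MP or MT, untaught and with full effect. Any power figure built on it rests on an assumed dilution, and shrinking the effect equally at all visits ignores that T2 is untouched.
- **That control patients keep the sheets until week 12.** The intervention lasts six weeks, and retention of the sheets is not described.

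**Conclusion.** The contradiction holds as written. The hand-out and diary rule covers all patients, while the movement tasks and the difficulty rating are defined for MP and MT, and control patients are assigned relaxation. Followed literally, it gives control patients part of the experimental content for 6 of 30 sessions. It could dilute the MP-control and MT-control contrasts at T3 and T4; T2 and the MP-MT contrast are not affected.

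The direction rests on one assumption: that any use of the sheets by control patients works the same way as the interventions. The effect would then be to understate a benefit over control, not to create one. The size cannot be estimated from the documents, and whether any contamination took place is unknown. The point deserves correction because it bears on what the comparator is and the remedy is simple.

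**What to change.** 1. Reconcile the hand-out and diary sentences with the control definition by restricting the movement-task sheets and the difficulty log to the MP and MT arms.
2. State what written material the control arm receives for its unguided relaxation sessions, and what its diary records.
3. Check which sheets and diaries already enrolled control patients were given, and report the number who received movement-task sheets. The Discussion describes recruitment as still under way, so this can be done before results are reported.

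The cost is a short text change, a separate control hand-out and diary, and a records check. If the check shows that only MP and MT patients received the sheets, correcting the description is enough. If some control patients received them, the report should say so when interpreting the contrasts with control at 6 and 12 weeks.
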